#### 5.2.1 Epochs

Before calculating IBS, we will segment the neural data from each phase into 30-second epochs, as described in Nguyen et al. (2021b). These 30-second epochs allow us to observe the change in IBS over time. As well as its use in prior neuroscience studies, 30 seconds is the time period used in our prior work estimating rapport, facilitating the behavior analysis pipeline we describe below.

#### 5.2.2 Inter-brain synchrony

Inter-brain synchrony will be calculated using wavelet transform coherence (WTC), which allows comparison of similarity between signals in terms of spectral content (Czeszumski et al., 2020). WTC calculations will be conducted using the hyperscanning Python pipeline (HyPyP) developed by Ayrolles et al. (2021), across six regions of interest (left and right PFC, left and right TPJ, left, and right STS) within the low-frequency range 0.01 to 0.15 Hz. This range is chosen to filter out respiration and heart rate while still allowing a relatively wide range of frequencies implicated in free verbal interaction in prior work (specifically Mayseless et al., 2019; Nguyen et al., 2021b). Like these previous authors, however, we will carry out visual inspection and spectral analyses and add higher frequencies if motivated by the data.

For each dyad, we will obtain IBS values for each 30 second epoch and each ROI pair. We will also compute the average IBS across each 8–10 min phase of the experiment. In total, we will thereby obtain IBS values for each dyad, from each ROI, for the entire phase and for each 30-second epoch within that phase. To best capture the IBS evoked by social interaction, we normalize the values of the social phase by computing a Z-score, i.e., removing the average value of the solo phase and dividing by the standard deviation. This process is repeated for each dyad. To compare the difference between phases, then, we run a general linear model (GLM). Normalized IBS values are entered as the dependent variable with interactive phases (i.e., collaboration and discussion) and the interaction effect of ROIs (six per dyad) as fixed factors. To assess whether the observed neural activity is most likely due to exchanges between the children, as opposed to being primarily driven by the content of the task, we will also generate random pairings by calculating IBS with false dyads (the child's time-series paired to the time-series of another child coming from a different dyad during the same phase). We will create multiple such random pairs to generate the distribution of IBS expected under the null hypothesis (H0) (Nguyen et al., 2021a). The values of the actual real pairs will then be compared to these H0 distributions, thus providing an empirical *p*-value. An example of this analysis is illustrated for the feasibility study in Figure 5B. We will also generate a more conservative intra-pair comparison based on temporally shuffled behavior. In this case, the participants stay the same but the epochs are randomized to generate false dyads (Ayrolles et al., 2021).

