Because of the complexity of recruitment for longitudinal studies, and particularly those using neuroscientific methods with children, we will start by collecting data with 9–10-year-old dyads, and expect to analyze and publish the results from that work while collecting data from other age groups.

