### 5.2 fNIRS data pre-processing

For each subject, raw data will be visually inspected for evidence of artifacts that would result in poor data quality. Pre-processing will be carried out by MNE-NIRS, a dedicated Python library for pre-processing fNIRS data (Luke et al., 2021). To further enhance data quality, for each source-detector pair, the impact of systemic physiological factors will be attenuated by performing short-channel regression using the temporally embedded Canonical Correlation Analysis (von Lühmann et al., 2020). Raw intensity values will be converted into optical density values and then motion-corrected using temporal derivative distribution repair (Fishburn et al., 2019). The scalp coupling index (SCI), a measure of signal strength between the optodes and the scalp (Pollonini et al., 2014), will then be calculated for each of the 42 channels for the entire experiment. Any channel with an SCI value lower than 0.8 will be excluded from subsequent analysis (Pollonini et al., 2016). For the subsequent dyadic neural synchrony calculations (described further below), only shared channels with sufficient SCI will be used. Remaining data will then be converted into hemoglobin concentration values using the modified Beer-Lambert law (Baker et al., 2014). Data will be filtered in order to remove heart rate and respiration artifacts by applying a band-pass filter between 0.01 and 0.5 Hz (Yücel et al., 2021). Both oxygenated hemoglobin (HbO) and deoxygenated hemoglobin (HbR) will be analyzed, as HbO exhibits greater sensitivity to changes in cerebral blood flow (Jiang et al., 2012), while NIRS data acquired during verbal communication is most accurately represented by the HbR signal (Zhang et al., 2017), since speaking can influence end-tidal CO2 blood levels (Scholkmann et al., 2013).

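### The inter-brain synchrony band, set low to exclude respiration, may be widened upward after looking at the data, with no limit or blinding stated

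*Protocol article*

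**What the plan says.** Section 5.2.2 (Inter-brain synchrony) computes wavelet transform coherence in six regions of interest "within the low-frequency range 0.01 to 0.15 Hz". The reason is given directly: "This range is chosen to filter out respiration and heart rate while still allowing a relatively wide range of frequencies". The next sentence, citing earlier authors as precedent, says that "we will carry out visual inspection and spectral analyses and add higher frequencies if motivated by the data".

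Section 5.2 (fNIRS data pre-processing) removes heart rate and respiration artefacts by "applying a band-pass filter between 0.01 and 0.5 Hz". It also states that "the impact of systemic physiological factors will be attenuated by performing short-channel regression".

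Further on in Section 5.2.2, IBS becomes an outcome: "Normalized IBS values are entered as the dependent variable with interactive phases". Real pairs are compared with false dyads, and also with shuffled epochs within the same pair.

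At the end of Section 4.2, the team will start with 9–10-year-olds and "expect to analyze and publish the results from that work while collecting data from other age groups".

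**The concern.** The band is part of the definition of IBS. A rule that lets it change once the study data have been seen lets the outcome be redefined from those data. The article does not say what would count as motivation, how far the band may go, whether the person deciding is blind to phase and pairing, or whether separate data are used. The false discovery rate correction in Section 6.6 is not tied to this choice.

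The permitted change also goes in only one direction, towards the frequencies that the band was set to exclude. Coherence from shared or coupled physiology could then be counted as neural synchrony.

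The reach is wide. IBS is predicted in Claim 1, aligned with rapport in Claim 2, tested for Granger causality in Claim 3, related to performance in Claim 4, used as edge strength in Claim 5 and compared across ages in Claim 6. The last of these needs the same quantity in all four age groups.

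**Working it through.** The plan gives no figure to reproduce here. Three checks were made.

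**1. What an extension can admit.** Inputs: analysis limit 0.15 Hz (Section 5.2.2) and filter limit 0.5 Hz (Section 5.2). Cycles per minute = Hz × 60.

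- 0.15 × 60 = 9 per minute.
- 0.5 × 60 = 30 per minute.

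The region open to extension is therefore 9 to 30 cycles per minute. The article gives no breathing rate. Assuming 15 to 25 breaths/min for children:

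- 15/60 = 0.25 Hz and 25/60 = 0.42 Hz.
- An extension to 0.20 Hz (12 per minute) admits none of this range. One to 0.30 Hz (18 per minute) admits part of it. One to 0.5 Hz admits all of it.

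With an assumed range of 15 to 30 breaths/min, respiration lies at 0.25 to 0.50 Hz and the picture is the same.

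**2. The two respiration statements side by side.** Section 5.2 credits the 0.5 Hz filter with removing respiration. Section 5.2.2 relies on 0.15 Hz for the same purpose. A filter that passes everything up to 30 cycles per minute does not by itself remove breathing slower than that. On the assumption above, the exclusion is done by the 0.15 Hz limit, and that is the limit the rule allows to be raised.

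**3. Illustrative effect on the error rate.** Assumptions: two-sided 5% test; the better of the original band and one wider band containing it is kept; each unit of frequency contributes independently, on a linear or a logarithmic scale. For upper limit U, the correlation between the two test statistics is

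- linear: r = √[(0.15 − 0.01)/(U − 0.01)]
- logarithmic: r = √[ln(0.15/0.01)/ln(U/0.01)]

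The false-positive rate is P(|Z₁| > 1.96 or |Z₂| > 1.96) for bivariate normal statistics with that r.

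| U (Hz) | r, linear | rate | r, log | rate |
|---|---|---|---|---|
| 0.20 | 0.858 | 7.4% | 0.951 | 6.5% |
| 0.30 | 0.695 | 8.4% | 0.892 | 7.1% |
| 0.50 | 0.535 | 9.0% | 0.832 | 7.6% |

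The range is about 6.5% to 9%, against 5% when one band is fixed in advance.

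**The case against.** The strongest reply is that this is ordinary signal-processing practice with precedent, and that the detailed criteria belong in a fuller document not shown here. Inspecting spectra is also not the same as choosing by test result. That last point stands: inspection blind to condition would be defensible, and the error figures apply only if selection follows results. But the article does not limit the inspection in this way. What it prints is itself a data-dependent rule, so the problem is more than missing detail.

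The plan does have safeguards. Short-channel regression targets systemic physiology, deoxygenated haemoglobin is analysed alongside oxygenated haemoglobin partly because of speech effects, and the solo phase used for normalisation is itself spoken aloud. These reduce the risk. However, short-channel regression is said only to attenuate. Physiology coupled between partners would be present in real pairs and absent or misaligned in false dyads and shuffled epochs, so neither comparison would remove it.

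Four stronger readings are tempting but not supported:

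- A reader might infer that any widening brings respiration back. That depends on its width, which the text leaves open.
- A reader might treat the bands as two or three independent tests and infer a near doubling or tripling of the error rate. A widened band contains the original, so independence does not apply.
- A reader might infer that breathing coordinated through turn-taking is the likeliest trigger for widening. The article offers no evidence on this.
- A reader might infer that the band will be re-chosen by age. The text does not say so, and the Claim 6 model across four groups presupposes a common definition. The text simply does not guarantee one.

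**Conclusion.** The point holds as a contradiction and a badly fixed outcome definition. Section 5.2.2 justifies its upper limit by the need to exclude respiration and then allows that limit to be raised from the study's own data, with 0.5 Hz as the only cap. Whether respiration actually enters depends on the width chosen and on the assumed breathing rate. The inflation to roughly 6.5–9% is an illustration that rests on the nested-band model and on selection by results. The wording of Section 5.2 on respiration is wrong under the same breathing-rate assumption, but this matters little while the analysis limit stays at 0.15 Hz. Because one cohort is analysed and published early, the band should be settled before that analysis.

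**What to change.** - In Section 5.2.2, fix 0.01 to 0.15 Hz for all confirmatory IBS analyses in all four age groups, before any 9–10-year-old data are analysed.
- State that results from added higher frequencies will be reported separately, as exploratory or sensitivity analyses.
- In Section 5.2, credit the exclusion of respiration to the 0.15 Hz analysis limit, with short-channel regression attenuating what remains, and not to the 0.5 Hz filter.

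The cost is a few sentences and no change in sample size. With one fixed band, this choice adds nothing to the 5% error rate of each test. The downside is that a genuine effect above 0.15 Hz could be reported only as exploratory.

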### 4.1 Target population and sample

An *a priori* power analysis was conducted using G^*^Power 3.1.9.7 (Faul et al., 2007) to determine the sample size needed for the study. The analysis was based on an ANOVA with 4 age groups and 6 measurements, using an effect size of (d = 0.24), based on our pilot study results, and an alpha of 0.05. The results indicate that a total sample size of 176 dyads will be required to achieve a power of 0.95. This aligns with the recommendation of Bizzego et al. (2022), who suggested a minimum sample size of *N* = 150 to detect significant IBS. There are significant challenges in recruiting participants for hyperscanning experiments, and particularly for recruiting dyads of unfamiliar children. In the event of a smaller sample size, we can adopt an analytical approach, such as the non-parametric bootstrap test with a pooled resampling method, as proposed by Dwivedi et al. (2017), and cited in Bizzego et al. (2022), which has demonstrated satisfactory performance in cases of small sample sizes and non-normally distributed data. We will enlist equal numbers of dyads from 4 age groups: 5–6, 7–8, 9–10, and 11–12 years (44 dyads per group). As social interaction may differ between boys and girls at these ages (Underwood et al., 1999), dyads will be of the same gender (both boys or both girls), and half of our participants will be male and half female (88 dyads of girls and 88 dyads of boys). As described above, in order to assess the initial building of rapport, all children will be strangers to one another. Our videoconference set-up will facilitate this, as we will set up video-conferencing in 2 different schools or after-school programs.

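### The within-pair epoch shuffle is labelled more conservative without qualification, but against task- or time-driven synchrony it is the more liberal of the two nulls

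*Protocol article*

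**What the plan says.** Section 5.2.2 of the protocol article asks whether synchrony comes from exchange between the children, "as opposed to being primarily driven by the content of the task". Its first comparison builds false dyads in which a child's series is "paired to the time-series of another child coming from a different dyad during the same phase". Many such pairs form a null distribution, and the real pairs receive an empirical p-value against it.

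The second comparison follows at once: "We will also generate a more conservative intra-pair comparison based on temporally shuffled behavior". In it, "the participants stay the same but the epochs are randomized to generate false dyads". No reason is given for the label, and no separate rival explanation is named for this null.

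Section 5.2.1 sets the unit that is shuffled: "we will segment the neural data from each phase into 30-second epochs". Section 4.2 adds another control, the contrast between solo and collaborative work, intended to rule out synchrony from viewing the same stimuli.

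**The concern.** A null is conservative only with respect to a particular rival explanation. The one named in this part of the plan is synchrony driven by the task. Shuffling pairs one child's epoch i with the other child's epoch j. Whatever both children do because they are at the same point of the same phase, such as reacting to its onset, is then absent from the null but present in the real value. The null sits too low, and real pairs can exceed it although neither child influences the other.

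The risk is in interpretation. If the two tests disagree, the label tells the reader to trust the shuffle, which is the wrong one to trust when the doubt concerns shared task or timing effects.

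**Working it through.** The plan gives no figure on this point, so there is nothing to reproduce. The check has three steps.

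**1. What each null keeps.** Write a child's signal in epoch i as s(i) + r(i) + h + noise. Here s is a response common to all children at that time in the phase, r is coupling specific to the dyad, and h is stable similarity of the two children's signals.

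| | s | r | h |
|---|---|---|---|
| Real pair | kept | kept | kept |
| Random pair, same phase, time-aligned | kept | removed | removed |
| Same pair, epochs shuffled | removed | removed | kept |

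Real minus random pair therefore responds to r and h. Real minus shuffled responds to s and r. Only r is exchange.

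**2. Simulation.** Inputs from the document:
- "44 dyads per group" (section 4.1).
- 30-second epochs (section 5.2.1).
- Phase length from "We will also compute the average IBS across each 8–10 min phase of the experiment", that is 16 to 20 epochs; 16 were used.
- Wavelet coherence "within the low-frequency range 0.01 to 0.15 Hz". The simulation used 0.035 to 0.14 Hz, because a 30-second epoch holds no full cycle below 1/30 = 0.033 Hz.

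Assumptions:
- One-sided alpha of 0.05. The document states 0.05 only for the power analysis.
- AR(1) noise with coefficient 0.7, sampled at 1 Hz.
- Test statistic: mean coherence over dyads.
- False dyads aligned from phase onset.
- SD of the added component k = 0.3 or 0.5 times the child's own noise SD. Its share of variance is k²/(1 + k²): 0.09/1.09 = 8.3% and 0.25/1.25 = 20%.

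There were 199 null draws per test and 150 simulated studies per row. The Monte Carlo standard error, √(p(1 − p)/150), is 1.8 points at 5% and 4.1 points at 50%.

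| Scenario | Random pairs reject | Shuffle rejects |
|---|---|---|
| No signal | 4.0% | 3.3% |
| Shared throughout phase, no exchange, k = 0.3 | 6.0% | 15.3% |
| Same, k = 0.5 | 8.0% | 84.7% |
| Shared onset transient only, no exchange, k = 0.3 | 2.7% | 58.0% |
| Same, k = 0.5 | 6.7% | 100% |
| Stable dyad similarity, no coupling, k = 0.5 | 100% | 18.7% |
| True dyad-specific coupling, k = 0.5 | 88.7% | 88.0% |

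The onset rows assume a strong local response. The transient was scaled over the whole 480 s but lies in the first 60 s, so its root mean square there is k × √(480/60) = 2.83k, or 0.85 and 1.41 noise SDs.

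A second simulation with other settings (9-minute phase, 18 epochs, 0.04 to 0.15 Hz, 44 dyads, 150 trials) agrees. At shared components of 10%, 15% and 20% of variance the shuffle rejected in 19%, 48% and 84% of trials, and time-aligned false dyads in 3% to 6%.

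**3. Requiring both nulls.** The joint rejection rate cannot exceed the smaller of the two rates. Without exchange it is at most 6.0% and 8.0% (shared throughout), 2.7% and 6.7% (onset) and 18.7% (stable similarity). With true coupling it is at least 88.7 + 88.0 − 100 = 76.7% and at most 88.0%.

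**The case against.** The label has a sound basis. Section 4.1 makes real dyads same-gender and recruits them within age groups, while section 5.2.2 restricts random partners only to the same phase. Real pairs could then exceed random pairs merely because the two children are alike. The shuffle guards against this, and in that scenario it falsely rejected far less often (18.7% against 100%). This stands, and it is why the shuffle should be kept. Two limits apply: 18.7% is still above 5%, and the simulated similarity (both children sharing one exact frequency) is probably stronger than age and gender matching would produce.

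The shuffle is also a supplement. The random-pair test with its p-value, the solo contrast and the normalisation of the social phase to the solo phase all remain. This stands and limits the harm.

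The plausible shared drivers are few. The only wrap-up prompt described in section 4.2 is conditional and belongs to the solo phase. No mid-phase change of image is described, and the social phase is free talk. A drift over 8 to 10 minutes (1/480 to 1/600 Hz, about 0.002 Hz) falls below the 0.01 Hz cut-off. Phase onset is the main route left, and its size is unknown.

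A reader might infer that the shuffle defeats its own stated purpose, or that the plan will rest its conclusion about exchange on it. The documents do not support either reading. The clause about task content introduces the random pairs. That it also covers the shuffle is the natural reading, but it is not stated, and no decision rule relies on the shuffle alone.

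**Conclusion.** The point holds as a labelling and interpretation error. The shuffle is stricter only against stable child- or dyad-level similarity. Against synchrony from task content or time in phase, the rival explanation named in the same section, it is more liberal. Neither null dominates.

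The direction follows from how the two nulls are built. The size does not: the false rejection rates of 15% to 85% for the shuffle, against 6% to 8% for random pairs, rest on an assumed shared component of 8% to 20% of variance and on false dyads being aligned from phase onset. With no shared component both tests hold about 5%. The existing random-pair test is not invalidated, though it has its own gap while partners are unmatched on age and gender. The correction is worth making because it is cheap and governs how a disagreement between the two tests would be read.

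**What to change.** In section 5.2.2:
- Delete the words *more conservative* and state which explanation each null excludes: time-aligned random pairs for task content and time in phase, the shuffle for stable similarity of the two children.
- Draw false dyads from the same age group, gender, task, week and phase, aligned at the same epoch index.
- Attribute IBS to exchange only if real pairs exceed both nulls. Report rejection of the shuffled null alone as time-locked coupling, not as evidence of exchange.
- Optionally, subtract the across-children mean time course before shuffling. In the second simulation this brought the shuffle's false rejection to 5% to 9%, but it also removes some genuine coupling that occurs at the same moment in most dyads.

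Cost: a few sentences, a slightly stricter criterion and a smaller pool of false dyads. The pool remains adequate. If gender is balanced within each age group (an assumption; the document gives 88 girl and 88 boy dyads overall), a cell has 22 dyads and 44 children. That gives 44 × 43/2 − 22 = 924 possible false dyads per cell, before any loss of data.

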**Figure 2 F2:**
[figure not shown]
**(A)** Representative set-up of one of the experimental rooms (here in the feasibility study). **(B)** fNIRS montage showing the regions of interest: PFC (blue channels), STS (yellow channels), and TPJ (green channels). Red and blue circles represent the sources and detectors, respectively.

### 5.3 Behavioral annotation

We argued above that it is not sufficient to focus on one single conversational behavior, nor one single modality of conversational behaviors, in order to understand the ways in which the behaviors of social interaction are related to IBS. Here we describe how we acquire the multimodal data. Conversation is influenced by the situational context (e.g., classroom vs. playground, brainstorming vs. class presentation), and by the interlocutor (e.g., adult vs. child, stranger vs. friend or family member). These differences underscore the importance of rigorous annotation, including using automatic extraction based on advances in signal processing to allow efficient treatment of large amounts of data, as well as hand annotation using coding manuals tested and normed for the culture and age group in question.

In terms of the automatic extraction of nonverbal behavior, we will employ OpenFace, a widely-used open-source computer vision framework that utilizes action units (AUs) to detect facial landmarks, allowing us to detect facial expressions in video (Baltrusaitis et al., 2018). AUs are translated into behavioral features such as smiles. This allow us, for example, to differentiate between the Duchenne or genuine smile and the polite smile (Ekman et al., 1990). We will next perform a manual check on 10% of the data at each age using the ELAN video annotation tool (Wittenburg et al., 2006) to ensure that the behaviors are correctly annotated by the software. We have conducted such checks in the past, and have found alignment between high inter-rater reliability hand annotation and OpenFace. If, however, this is not the case for these data for any reason, we will fine-tune the software with the annotated data to ensure alignment and then retest on a second sample of 10%. Second order behaviors (e.g., mutual smiles) will then be automatically extracted. Assessment of eye gaze in the videoconference-mediated conversations will be achieved using the framework developed by Tran et al. (2022) applied to the raw eye gaze data generated by OpenFace. This application enables the extraction of eye gaze direction employing a dynamic clustering algorithm. As with facial expression, we will then automatically extract the second-order behavior of mutual eye gaze.

In addition to non-verbal behavior, we will also extract prosodic features (e.g., pitch, loudness and speaking rate), which have also been shown to play a role in rapport management (Grimberg et al., 2022). These features will be extracted using a widely used open source audio analysis framework called OpenSmile (Eyben et al., 2010), which enables acoustic features in the audio to be extracted and then interpreted as prosodic features such as intonation, speech rate, and loudness. We will then automatically extract the second order behaviors (e.g., identical speech rate, entrainment of loudness, etc.).

Finally, we will annotate verbal or linguistic behaviors using the Elan software package, version 6.7 (Wittenburg et al., 2006), concentrating specifically on what are called conversational strategies—ways of speaking that serve particular interpersonal functions (such as using praise to “soften up” one's interlocutor, or hedges to avoid embarrassing the other person), that have been shown to play a role in building rapport among adults and young people (Zhao et al., 2014; Madaio et al., 2018). Our coding scheme for conversational strategies, refined and published in numerous papers over the last decade, is based on behavioral phenomena that have been shown in work by others and by our own team to impact rapport. Each coding scheme treats one verbal behavior. In the current work, we will annotate self-disclosure (revealing details about oneself that are not publicly available, such as “I love dogs”), reference to shared-experience (referring to an event that was engaged in together, such as “last week's problem was really hard, right?”), praise (such as “you're better at this than me”), and backchannels (sounds or words that indicate that the listener is following, such as “uh huh” or “yeah”). We will then use a grounded theory (Glaser and Strauss, 1967) bottom-up approach on a subset of the data from each age to understand if we have missed any relevant conversational strategies in the dataset and we will add them to the annotation scheme if so. Following this, we will automatically extract second-order conversational strategies, such as mutual self-disclosure (“I love dogs.” “Me too”). Annotation of conversational strategies will be carried out by experienced annotators whose inter-rater reliability on Krippendorf's alpha must be above 0.7 before they proceed to annotating independently (Krippendorff, 2011). Importantly, we will annotate only what is visible, and then correlate with the underlying dyadic psychological state of rapport, rather than placing annotation of putative underlying states such as beliefs (e.g., this child likes her partner), feelings (she looks happy), and/or intentions (she wants to convince the other child that she's right) on the same level as visible behaviors.

